#### Sample size

Historical data suggested that annual recruitment to the large centres would be 14 patients, with 9 patients in each of Bristol and Birmingham and 3 in Newcastle. The sample size was determined to detect a ratio of the SDs under the standard therapy and NIDUS of three, with power at least 80% and two-sided type I error of 5%. A threefold improvement in the precision of fluid removal in this population would be sufficiently marked that it would be likely to change practice. The calculation used the methods in Matthews and Forbes,^26^ adapted to unequal cluster sizes, and found that four periods in the SW design, each of 4.5 months, gave a power of 80% with an assumed intraclass correlation coefficient (ICC) of 0.1% and 84% for an ICC of 0.05. It was believed that these represented conservative choices for the ICC.

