**Methods and analysis:**

The clinical investigation is taking place in six UK centres. This is a randomised clinical investigation using a cluster stepped-wedge design. The study aims to recruit 95 babies requiring renal replacement therapy in paediatric intensive care units over 20 months.

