### Statistical considerations

#### Primary outcome

The primary aim is to compare the precision of the standard therapy and NIDUS to deliver the fluid removal rate prescribed by the treating physician. The primary outcome is based on the first available determination of fluid removal over a period exceeding 1 hour and within the first 48 hours of commencement of RRT: if the observed removal is *X* and the prescribed removal is *A*, the primary outcome is log|*X-A*|. The expected difference of this quantity between the treatment groups is the log of the ratio of the SDs of the determinations by the two methods. The method supposes that *X* follows a normal distribution with mean *A* and hence the variance of the outcome is 
$\pi^{2}/8$
.

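### The stated power of at least 80% has no margin at the larger planning ICC: it needs a primary outcome from every expected recruit and an idealised variance, and it was not computed for the fixed-cluster model now planned

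*Protocol article*

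**What the plan says.** The Sample size section states the target effect, "The sample size was determined to detect a ratio of the SDs under the standard therapy and NIDUS of three", and the requirement, "with power at least 80% and two-sided type I error of 5" per cent. Recruitment is taken from history: "annual recruitment to the large centres would be 14 patients, with 9 patients in each of Bristol and Birmingham and 3 in Newcastle". The result is that "four periods in the SW design, each of 4.5 months, gave a power of 80" per cent with "an assumed intraclass correlation coefficient (ICC) of 0.1% and 84% for an ICC of 0.05". Both ICCs are described as conservative.

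The abstract gives the target: "The study aims to recruit 95 babies requiring renal replacement therapy in paediatric intensive care units over 20 months". Table 1 repeats a size of about 95.

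Under Primary outcome, the endpoint is log|X−A|, taken from the "first available determination of fluid removal over a period exceeding 1 hour and within the first 48 hours of commencement of RRT". Its variance comes from an assumption: X "follows a normal distribution with mean *A* and hence the variance of the outcome is" π²/8.

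Under Planned analysis, all available data are analysed with fixed effects for treatment, period and cluster. The fixed cluster effect is explained as a response to the COVID-19 interruptions. Sensitivity analyses will examine the assumptions about X.

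**The concern.** Three features leave the stated power without reserve.

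- **Completeness.** The recruitment target equals the number of babies in the power calculation. Nothing is added for babies without a weighed determination of more than 1 hour in the first 48 hours, although the outcome is defined by availability.
- **Variance.** π²/8 is exact when every baby in an arm within a centre has the same SD of fluid-removal error. Weights run from 0.8 to 7.99 kg, and the control arm mixes peritoneal dialysis with CVVH, so one common SD is doubtful.
- **Model.** The calculation is indexed by an ICC, so it rests on a random cluster effect. The primary analysis now uses a fixed one, and no power is given for it.

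At stake is how the trial describes its own sensitivity. If 95 recruits are read as securing 80% power, a null result may be given more weight than the design supports.

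**Working it through.** **Inputs**
- Effect: ln 3 = 1.0986 on the log|X−A| scale; two-sided 5%, z = 1.96 (Sample size).
- Residual variance: σ² = π²/8 = 1.2337 (Primary outcome).
- Recruitment: 3×14 + 9 + 9 + 3 = 63 a year. Four periods of 4.5 months are 1.5 years, so 63 × 1.5 = 94.5 babies. Per centre and period (× 0.375): 5.25, 3.375 and 1.125.
- Three sequences, each with one large and one small centre (Randomisation). The text does not say which small centre is in which sequence.

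**Formula.** For a centre with n babies per period, the covariance of its four period means is V = (σ²/n)·I + τ²·J, with I the identity matrix, J the matrix of ones and τ² = σ²·ICC/(1−ICC). The information, sum of X′V⁻¹X over the six centres (treatment and four period effects), is inverted to give the SE of the treatment effect. Power = Φ(ln 3/SE − 1.96).

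**Reproducing the stated figures** (all 94.5 babies, smallest centre in the middle sequence)
- ICC 0.10: τ² = 0.1371, SE = 0.3902, power = Φ(2.816 − 1.96) = 80.4%.
- ICC 0.05: τ² = 0.0649, SE = 0.3729, power = Φ(2.946 − 1.96) = 83.8%.
- ICC 0.001 (0.1% as printed): SE = 0.3368 to 0.3501 by placement, power 90.4% to 88.1%. This does not give 80%.
- Smallest centre first or last: 78.6% (ICC 0.10) and 81.7% (ICC 0.05).
- Taking π²/8 as total rather than residual variance gives 82.6–84.3% and 83.6–85.6%, which does not fit the stated pair.

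The best match is therefore the first set, with no allowance for loss.

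**Missing outcomes** (n multiplied by 1 − loss; loss rates assumed; smallest centre in the middle sequence)

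| Loss | ICC 0.10 | ICC 0.05 |
|---|---|---|
| 0 | 80.4% | 83.8% |
| 1 baby | 80.0% | 83.5% |
| 2 babies | 79.7% | 83.1% |
| 5% | 78.6% | 82.1% |
| 10% | 76.7% | 80.3% |
| 20% | 72.3% | 76.1% |

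The 80% line is reached at about 1 missing baby (1.1%) for ICC 0.10 and about 10 (10.8%) for ICC 0.05.

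**Spread of SDs between babies.** If X is normal with mean A and a baby-specific SD σᵢ, then log|X−A| = log σᵢ + log|Z|, with Z standard normal. The variance becomes π²/8 + Var(log σᵢ). Suppose log σᵢ is normal and the 5th–95th centile range of SDs is threefold. Then Var(log σᵢ) = (ln 3/3.29)² = 0.11. With complete data and τ² held fixed, power is 77.3% (ICC 0.10) and 81.0% (ICC 0.05). Adding 10% loss gives 73.5% and 77.3%.

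**Fixed cluster effects.** Replace τ² by six centre indicators, with the same cell sizes and σ² = π²/8. SE = 0.4310 (smallest centre in the middle) or 0.4379 (first or last). Power = Φ(2.549 − 1.96) = 72.2%, or 70.9%, with complete data and whatever the ICC. With 10% loss it is 67.7% or 66.3%; with 20%, 62.5% or 61.2%.

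**The case against.** The stated figures are not miscalculated: they reproduce, and with complete data and the stated variance the random-cluster design has the power claimed. A reader might infer that any missing determination or any spread in SDs takes the trial below 80%. The documents do not support that. The article gives two ICCs, and at 0.05 power stays at or above 80% with about 10% loss or with a threefold spread. Even at 0.10, one missing baby leaves 80.0%.

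Other points against also have weight:
- Loss rates and spreads are not in the article. The outcome needs only one determination in 48 hours, which should limit missingness.
- π²/8 is a floor only for normal errors centred on A with SDs that differ between babies. Other shapes can lower it: if |X−A| is uniform, the variance of its log is 1.0.
- The ICC already carries differences between centres, so only spread within a centre is uncovered.
- The actual sequence of the smallest centre is not visible, so 78.6% is a possibility and not a demonstrated fault.
- Planned sensitivity analyses address the assumptions about X. They protect validity but do not restore power.

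Twenty months of recruitment at 63 a year would yield 105 babies, which could look like a cushion. But the target is 95 and the power is tied to four periods of 4.5 months, so the article does not claim those extra babies.

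What stands is that the 80% case has no reserve, its ICC is apparently misprinted, and neither quoted power applies to the model now planned.

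**Conclusion.** The point holds as one about margin and description; it does not show an arithmetic error. At ICC 0.10 the promise of at least 80% rests on essentially every expected recruit being evaluable, with a margin of about one baby. Assumed losses of 5–20% bring power to 78.6–72.3%, and an assumed threefold spread of SDs to 77.3%. At ICC 0.05 there is slack for about 10% loss. These figures rest on reading 0.1% as 0.10, on the smallest centre being in the middle sequence, and on assumed loss and spread.

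The fixed-cluster result of about 71–72% needs no assumption about loss or spread. It uses the article's own recruitment, variance and effect, and it is the more consequential figure because it concerns the analysis now intended. It is not evidence that the original calculation was wrong, since the model was changed in response to the COVID-19 interruptions.

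**What to change.** In the Sample size section:

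1. Correct the printed ICC, presumably to 0.1.
2. State that 80% and 84% apply to about 95 babies with a usable primary outcome, under the random-cluster calculation.
3. Give power at 90% and 80% completeness, and under the fixed-cluster model, using the actual placement of centres.
4. Report progress as evaluable babies alongside recruits.

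The 62 control babies reported under Recruitment can be used to check completeness and whether the residual variance (within centre and period) is near π²/8 in the control arm. This reveals no treatment comparison. Because that arm mixes peritoneal dialysis with CVVH, its variance should be quoted as a sensitivity figure and should not replace π²/8 for both arms.

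The cost is a short calculation on data in hand and a less favourable stated power. No extra patients and no change in procedures are needed.

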### Study design

The study uses a cluster randomised standard stepped-wedge (SW) design^25^ with four periods and three sequences (figure 1). The control periods use conventional therapy (PD or CVVH), with NIDUS used in intervention periods. Each site will be trained in setting up and using the NIDUS before switching to an intervention period. The design means that all participating centres will have the chance to use both treatments during the course of the study. PICU nurses will need to be competency assessed before each site can begin using the intervention; 24 hours on call nurse/clinician is provided from Newcastle for telephone support. Using an SW design permits the phased training on NIDUS and allows within-centre comparisons to contribute to the treatment estimate.

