### Randomisation

Past records suggested that Great Ormond Street Hospital, Evelina and Southampton (the large centres) treat substantially more patients for RRT than Birmingham, Bristol and Newcastle (the small centres). To avoid large imbalances between the sequences, random permutation in R software was used to allocate one large and one small centre to each sequence. The statistician was blind to the identities of the centres during the allocation.

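### The stated power of 80% at an ICC of 0.1% and 84% at an ICC of 0.05 cannot both hold; 0.1% is most likely a misprint for 0.1

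*Protocol article*

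**What the plan says.** The Sample size section reports two results for the chosen design. The first is that "four periods in the SW design, each of 4.5 months, gave a power of 80% with an assumed intraclass correlation coefficient (ICC) of 0.1", where the article prints a percent sign directly after the last figure. The second is a power of 84% at an ICC of 0.05. One ICC is therefore a percentage and the other a proportion. The next sentence covers both: "It was believed that these represented conservative choices for the ICC".

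The other inputs are also in the article:

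- Study design: "The study uses a cluster randomised standard stepped-wedge (SW) design^25^ with four periods and three sequences (figure 1".
- Randomisation: "random permutation in R software was used to allocate one large and one small centre to each sequence".
- Sample size, recruitment: "annual recruitment to the large centres would be 14 patients, with 9 patients in each of Bristol and Birmingham and 3 in Newcastle".
- Sample size, effect: "The sample size was determined to detect a ratio of the SDs under the standard therapy and NIDUS of three", with a two-sided 5% test and a power target of at least 80%.
- Primary outcome: the treatment difference is the log of the SD ratio, and the outcome variance is π²/8.

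**The concern.** As printed, a fifty-fold larger ICC (0.001 to 0.05) comes with four points more power. At small ICCs in a stepped-wedge design, comparisons between centres carry part of the information on treatment, and a growing ICC takes that information away. Power should therefore fall at first, not rise. The mixed units also suggest a slip in one of the two figures.

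The ICC is an assumed planning value. A reader who takes the sentence at face value would believe that the trial was planned on a negligible ICC and that a larger one does no harm. Anyone planning a similar trial could carry 0.001 forward. An ICC of 0.001 could also hardly be called conservative.

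**Working it through.** **Inputs.** The period length ("four periods in the SW design, each of 4.5 months") and the annual rates give the expected patients per centre and period:

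- large centre: 14 × 4.5/12 = 5.25
- Bristol or Birmingham: 9 × 4.5/12 = 3.375
- Newcastle: 3 × 4.5/12 = 1.125

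The total is 4 × (3 × 5.25 + 2 × 3.375 + 1.125) = 94.5. This agrees with the Abstract ("The study aims to recruit 95 babies requiring renal replacement therapy in paediatric intensive care units over 20 months"), so the rates are being read as the authors used them.

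The effect on the outcome scale is ln 3 = 1.0986, and π²/8 = 1.2337.

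**Model.** I used a stepped wedge with fixed period effects, a random centre intercept and unequal centre sizes. For centre i with m_i patients per period, the covariance of its four period means is V_i = (σ²/m_i)·I + τ²·J, where J is the 4 × 4 matrix of ones. The variance of the treatment effect is the treatment element of (Σ X_i′ V_i⁻¹ X_i)⁻¹, and power = Φ(1.0986/SE − 1.960).

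The article does not say which variance π²/8 is, so both readings were run for ICC ρ:

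- within-cluster: σ² = π²/8, τ² = ρ/(1 − ρ) × π²/8
- total: σ² = (1 − ρ) × π²/8, τ² = ρ × π²/8

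The text does not say which sequence holds the smallest centre, so all three positions were run. Sequences 1 and 3 give the same result.

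**Results, SE (power).**

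| ICC | Within-cluster, smallest centre in middle sequence | Within-cluster, smallest centre in outer sequence | Total, middle | Total, outer |
|---|---|---|---|---|
| 0.001 | 0.337 (90.4%) | 0.350 (88.1%) | 0.337 (90.4%) | 0.350 (88.1%) |
| 0.05 | 0.373 (83.8%) | 0.384 (81.7%) | 0.363 (85.6%) | 0.374 (83.6%) |
| 0.10 | 0.390 (80.4%) | 0.399 (78.6%) | 0.370 (84.3%) | 0.379 (82.6%) |

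**Attempt to reproduce the plan's figures.** A power of 80% needs SE = 1.0986/(1.960 + 0.842) = 0.392. At an ICC of 0.001 the SE is only 0.337 to 0.350, so power is 8 to 10 points above the printed value. A power of 84% needs SE = 1.0986/(1.960 + 0.994) = 0.372. At an ICC of 0.05 the SE is 0.363 to 0.384, so the printed 84% is within reach. The pair with 0.001 is not reproduced. The pair with 0.10 is closely matched in the first column: 80.4% and 83.8%.

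**Variants.** Rounding centre-period sizes to whole patients (N = 88) still gives 85.8–88.2% at 0.001. Equal centres, cluster autocorrelation of 0.5 to 0.9, a one-sided test, and periods of 4 or 5 months all leave power lower at 0.05 than at 0.001. A t reference with about 10 degrees of freedom brings power at 0.001 down to 80.7%, but then gives 75.4% at 0.05. No variant gives 80% at 0.001 together with 84% at 0.05.

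**The word conservative.** At an ICC of exactly 0, power is 90.5% (middle) or 88.3% (outer). Power at 0.001 is within about 0.2 points of that, so 0.001 is close to the most favourable value between 0 and 0.10.

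**The case against.** The strongest reply is that this is a stray percent sign. If the authors computed with 0.10, the 4.5-month periods, the 80% target and the recruitment of about 95 all stand. The primary analysis in the Planned analysis section uses fixed centre effects, so the ICC does not enter it, and a misprint changes no estimate. That reply is sound on consequence, but the printed figure is still wrong and needs restating.

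It is also fair that 0.10 is inferred. The match depends on π²/8 being the within-cluster variance and on the smallest centre being in the middle sequence. In an outer sequence the figures are 78.6% and 81.7%. The Primary outcome section calls π²/8 the variance of the outcome, which can be read as total variance. On that reading, power did not drop to 80% at any ICC tried with N = 94.5. The article's method was adapted to unequal cluster sizes in a way that is not shown.

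A reader might infer more than the documents support:

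- **That the trial is underpowered or the sample size miscalculated.** The match at 0.10 points the other way.
- **That power keeps falling at larger ICCs.** At 0.20 it is 75.5–77.0% on the within-cluster reading but 84.2–85.5% on the total-variance reading, which is no lower than at 0.10. The article fixes neither reading.
- **That the 80% depends on where the smallest centre was placed.** This is a feature of one variance reading. On the other, every placement exceeds 82% at 0.10.
- **That the claim of conservatism is wrong in itself.** It fails only for a literal 0.1%. Nothing in the article contradicts it for 0.05 and 0.10.

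**Conclusion.** The point holds in a limited form. The two power statements cannot both be right. At an ICC of 0.001 the design has about 88–90% power, not 80%, and power falls to 82–86% at 0.05. This rests on the article's own inputs and a standard random-intercept stepped-wedge model with a normal reference. It is the same under both variance readings and every placement of the smallest centre.

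The likely explanation is that 0.1 (10%) was meant, which makes the printed ICC one hundredth of the intended value. That explanation is well supported but not certain, because it depends on a variance reading and an allocation that the text does not give. The error lies in a reported planning assumption. Neither the sample size nor the planned analysis is shown to be wrong.

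**What to change.** Check the sentence against the original calculation and then do one of two things:

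- If 0.10 was used, restate the ICC for 80% power as 0.10.
- If 0.001 really was used, restate its power as about 88–90%.

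In either case, give both ICCs in the same unit. Keep the statement on conservative choices only for the corrected value; it should not stand beside 0.001.

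The cost is a look at the stored calculation and a correction to two sentences. The design, the sample size and the analysis do not change.

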### Planned analysis

Analysis of all available data will be on the basis of intention-to-treat. A subgroup analysis will compare NIDUS with conventional CVVH that is, excluding PD. For the latter group the amount of fluid removed (*X*) will be compared with the amount the machine reports to have been removed (*A*).

The primary outcome will be analysed using a linear model with fixed effects for treatment, period and cluster. The use of a fixed rather than random effect for cluster is a response to the interruptions to data collection due to the effect of COVID-19 on PICUs and the subsequent difficulty in defining a suitable dispersion structure. Sensitivity analyses will use a generalised estimating equation and will assess the assumptions about *X*. If these are untenable then *X-A* will be modelled directly, with treatment dependent variances for the error terms. The above linear model will be applied to the non-binary secondary outcomes. Binary outcomes will be analysed using generalised mixed models if possible but using simple tabulations if more sophisticated analyse are infeasible. Questionnaire data will be tabulated by treatment.

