### Recruitment

Recruitment, which commenced in December 2018, has been more rapid in the control period (62 total) than the intervention (ongoing) and the study has been impacted by the effects of the COVID-19 pandemic on NHS workload and staff availability. There have been three pauses to recruitment (May/June 2019; September/October 2019; November/December 2020) instigated urgently by the chief investigator related to problems identified at sites with the device and tubing/filter sets, to allow investigation and resolution. Medicines and Healthcare products Regulatory Agency (MHRA) temporarily withdrew notice of no objection in March 2020 while awaiting further information from the study team about anticoagulation, which coincided with the COVID-19 pandemic and recruitment to all non-COVID studies stopped; it was reinstated with additional clarification and no changes. Post-COVID-19 restart was in October 2020.

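### The 80%/84% power comes from a random-cluster calculation and does not carry over to the fixed-cluster primary analysis, which has about 71–72% power at the planned size

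*Protocol article*

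**What the plan says.** All references are to the protocol article.

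- **Sample size.** The target effect is stated thus: "The sample size was determined to detect a ratio of the SDs under the standard therapy and NIDUS of three". The error rates attached to that target are a power of 80% or more and a two-sided 5% level. Four periods of 4.5 months were then found sufficient, in that the design "gave a power of 80% with an assumed intraclass correlation coefficient (ICC) of 0.1% and 84% for an ICC of 0.05". The calculation is attributed to a published stepped-wedge method adapted to unequal cluster sizes.
- **Primary outcome.** The outcome is log|X−A|. The treatment difference on this scale "is the log of the ratio of the SDs of the determinations by the two methods". X is taken to follow a "normal distribution with mean *A* and hence the variance of the outcome is" π²/8.
- **Planned analysis.** "The primary outcome will be analysed using a linear model with fixed effects for treatment, period and cluster". The section explains that a fixed cluster effect was chosen over a random one because COVID-19 interrupted data collection and made a suitable dispersion structure hard to define.
- **Recruitment.** Accrual "has been more rapid in the control period (62 total) than the intervention (ongoing").

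The article gives no power figure for the fixed-cluster model. The target stays at about 95 babies.

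**The concern.** With a random cluster effect, the treatment estimate draws partly on differences between centres, so its precision depends on the ICC. With fixed cluster effects it uses only contrasts within centres, and between-centre information is lost. In a stepped wedge with six centres and four periods, that loss can be material.

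The article prints an ICC-dependent power and, two subsections later, a primary model to which that power does not apply. A reader will naturally take the 80% as describing the planned test. At stake is how a non-significant result is read: the type II error for a threefold gain in precision would be about 28–29% rather than at most 20%.

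**Working it through.** **Inputs**

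- Recruitment (Sample size): "annual recruitment to the large centres would be 14 patients, with 9 patients in each of Bristol and Birmingham and 3 in Newcastle". That is 3×14 + 2×9 + 3 = 63 a year. Per 4.5-month period this gives 5.25, 3.375 or 1.125 babies per centre; four periods give 63 × 18/12 = 94.5.
- Layout (Study design, Randomisation): three sequences and four periods, with one large and one small centre per sequence. The sequence holding the smallest centre is not stated, so every placement was tried. The two outer placements give the same result.
- Effect: log 3 = 1.0986.
- Variance: σ² = π²/8 = 1.2337, taken first as the within-cluster variance.
- Two-sided α = 0.05, so z = 1.96.

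**Formulae**

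Working with centre-by-period means, Var(treatment) is the treatment element of (Σₖ Xₖ′Vₖ⁻¹Xₖ)⁻¹, and power = Φ(1.0986/SE − 1.96).

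- Random cluster: Xₖ has treatment and period columns; Vₖ = diag(σ²/nₖ) + τ²J, where J is the matrix of ones and τ² = σ²·ICC/(1−ICC).
- Fixed cluster: Xₖ gains the cluster columns; Vₖ = diag(σ²/nₖ).

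**Step 1: reproduce the stated figures (random cluster)**

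| ICC | Smallest centre in middle sequence | Smallest centre in an outer sequence |
|---|---|---|
| 0.05 | SE 0.373, power 83.8% | SE 0.384, power 81.7% |
| 0.10 | SE 0.390, power 80.4% | SE 0.399, power 78.6% |
| 0.001 | SE 0.337, power 90.4% | SE 0.350, power 88.1% |

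The stated 84% and 80% match the middle placement at ICC 0.05 and 0.10. An ICC of 0.001, which is what 0.1% literally means, does not give 80% under either placement. In this model, moving from ICC 0.001 to 0.05 lowers power, whereas the sentence as printed has it rising from 80% to 84%. A misprint for 0.1 is the likely explanation.

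**Step 2: change only the cluster effect, from random to fixed**

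- Middle placement: SE 0.431; 1.0986/0.431 − 1.96 = 0.589; power 72.2%.
- Outer placement: SE 0.438; 1.0986/0.438 − 1.96 = 0.549; power 70.9%.
- With a t reference distribution: 69.9% to 71.2%.
- Ratio detectable with 80% power, exp{(1.96 + 0.842) × SE}: 3.35 (middle) and 3.41 (outer).

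The ICC does not enter here, so the doubt about 0.1% does not affect these results.

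**Step 3: vary the assumptions**

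- π²/8 as total variance, so that the within-cluster variance is (1−ICC)·π²/8: fixed-cluster power is about 73–74% at ICC 0.05 and 75–77% at ICC 0.10. This reading does not reproduce the stated 80%: the random-cluster model then gives 82.6–84.3% at ICC 0.10.
- 20 months of accrual at the stated rates (63 × 20/12 = 105 babies): 75–77%.
- Every centre-period rounded up to whole babies, which is a larger trial: 78–79%.

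**Step 4: the allocation in progress (fixed cluster, 62 controls, cells scaled proportionally within arm)**

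- 33 NIDUS babies (95 − 62): about 68–70%.
- About 47 NIDUS babies (half of 94.5): about 76–78%.

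**The case against.** A reader might infer that the claim of at least 80% power is simply false, or an arithmetic slip. The article does not support that. The Sample size section reports, in the past tense, how the size was chosen under a named ICC-based method, and its figures reproduce under that method. Nowhere does the article claim 80% for the fixed-cluster model. The switch is also disclosed and reasoned, so a design-stage calculation followed by a declared change of model is not in itself a contradiction.

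It can further be said that an updated power may sit in the full protocol or the SAP, neither of which is shown, and that restating power alters neither the estimate, nor its confidence interval, nor the test. Both points are fair and limit the consequence. They do not remove the defect: the article itself prints a power figure and a primary model, and the first does not describe the second.

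A reader might also infer from the 62 controls that power has already fallen to 68–70%. That does not follow. NIDUS recruitment was ongoing, and 33 is only what remains if the total stops at 95; recruitment nearer the planned number gives 76–78%.

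The reproduction has limits too. It needs 0.1% to be read as 0.1, it fits best with the smallest centre in the middle sequence, and the cited method could not be inspected. The random-intercept reading is therefore likely rather than certain.

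**Conclusion.** The point holds as a mismatch between the stated power and the planned primary analysis, not as an error in the design calculation. At the planned size, fixed cluster effects give about 71–72% power for an SD ratio of 3, and 80% power only for a ratio of about 3.35–3.41. This rests on three assumptions: the article's recruitment rates spread evenly over four equal periods, π²/8 as the within-cluster variance in both arms, and a normal reference distribution. The variance reading is the one that reproduces the stated figures; the alternative gives about 73–77%. No variant tried reached 80%, including those with more babies than planned. Proportional scaling of the cells ignores the recruitment pauses, so the figures for the actual allocation are indicative only.

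**What to change.** Revise the paragraph on power:

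1. Label 80% and 84% as the design-stage calculation for a random-cluster model.
2. Correct the ICC of 0.1% to 0.1, if that is the value used.
3. Add the power under the fixed-cluster primary model at the planned size (about 71–72% for a ratio of 3), or the ratio detectable with 80% power (about 3.4), and say whether π²/8 is the within-cluster or the total variance.
4. If power is given for the actual allocation, show it as a range over assumed NIDUS recruitment alongside 62 controls: about 68–70% with 33 and about 76–78% with about 47, cells scaled proportionally.

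The cost is one paragraph and a less favourable stated power. The design, the analysis model and the recruitment target stay as they are.
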